### Sample size and power calculation

Sample size calculation is based on the BSI, the primary clinical outcome variable in this study. We applied the mixed model ANOVA procedure described by Aberson [81], power of 0.80 and a two-sided alpha of 0.05.

We anticipated a medium-sized difference in effect size between MBT-IOP and MBT-DH based on prior research. In their RCT comparing MBT-IOP with structured clinical management, Bateman and Fonagy reported a within-group effect size for MBT-IOP of *d* =1.31 [29]. In their RCT comparing MBT-DH with usual care, the same authors reported a within-group effect size of *d* = 2.30 for MBT-DH at follow-up [26]. Hence, using an indirect comparison, the previous studies suggest at least a medium-size difference in effect (*d* = 0.50) between both treatment programmes. Applying seven repeated measures with a linear decrease of 0.5 SD more in MBT-DH than in the MBT-IOP group and an autoregressive intercorrelation structure with *r* = 0.50 between baseline and the last follow-up, 45 cases are needed in each group.

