### Statistical analyses

First, to investigate potential differences between the two groups at baseline, we will use parametric and nonparametric descriptive statistics, as appropriate. For the main analyses concentrating on primary and secondary outcomes, linear growth curve models for normally distributed outcome measurements will be used, logistic regression for binary data, and Poisson regression models for ordinal data. Results will be expressed in terms of comparison of the slopes for interval data, odds ratios for binary data, and incidence rate ratios for ordinal data. Furthermore, we will perform explorative analyses regarding predictors of differential treatment outcome. All analyses will be conducted according to intention-to-treat principles.

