## Discussion

Both MBT-DH and MBT-IOP have shown promise in the treatment of patients with BPD [2,15-19]. Yet, extant studies suggest that MBT-DH may be twice as costly as MBT-IOP. This cost difference makes MBT-IOP potentially a more cost-effective treatment than MBT-DH. On this basis, there is a need for an RCT comparing the efficacy and cost-effectiveness of MBT-DH and MBT-IOP.

The present paper outlines the study protocol for such a head-to-head comparison of MBT-DH and MBT-IOP in terms of their efficacy and cost-effectiveness in the context of a multisite study in the Netherlands. The study aims to answer a number of important questions in the field. First, this will be the first trial directly comparing the efficacy of MBT-DH and MBT-IOP. Second, this promises to be the first study that entails a state-of-the-art cost-effectiveness component for both MBT-DH and MBT-IOP. Given considerable differences in treatment intensity, and thus costs of the two treatment programmes, the results of this study promise to inform decisions not only concerning treatment referral, but also with regard to maximizing the use of health care resources in a climate of decreasing health expenditure. Another important goal of the final aim of the study, which focuses on predictors of change, is to provide information that will contribute to the optimization of treatment effects and health care resources. For instance, it may well be that both treatments have equal effectiveness and differ only in terms of cost. If this were the case, health care resources should be devoted to the less costly variant (probably MBT-IOP, due to its lower intensity). However, even if it is found that both treatments differ only in terms of their costs, there may still be a subgroup of patients that may need the more intensive intervention, MBT-DH, to derive benefit. In this scenario, MBT-DH would still be indicated as a cost-effective treatment in a subgroup of patients, and it would be crucially important to identify the features of this subgroup, to enable this intervention to be offered specifically to the patients who need this more intensive treatment format. Therefore, this study also aims to identify potential predictors of response to both MBT-IOP and MBT-DH, with the aim of facilitating treatment selection.

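### The stated 80% power at 45 per group does not follow from the protocol's own inputs: the planned slope comparison has about 65% power without baseline adjustment and about 77% with it

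*Protocol article*

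**What the plan says.** The Sample size and power calculation section bases the size of the trial on the BSI. It names its method ("We applied the mixed model ANOVA procedure", from a cited text) and its error rates ("power of 0.80 and a two-sided alpha of 0.05"). The effect is described as "Applying seven repeated measures with a linear decrease of 0.5 SD more in MBT-DH than in the MBT-IOP group". The correlation is autoregressive, with r = 0.50 "between baseline and the last follow-up, 45 cases are needed in each group". The section does not say which effect of the mixed ANOVA was powered.

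The Statistical analyses section plans growth curve models for normally distributed outcomes, and adds: "Results will be expressed in terms of comparison of the slopes for interval data". It neither includes nor excludes baseline adjustment.

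**The concern.** The article gives every input needed to check the sample size, and the output does not match them. In a first-order autoregressive process, the visits between the first and the last add almost nothing to the estimate of a linear slope. Seven measures are then worth little more than two, and the calculation collapses to a simple two-group comparison of a 0.5 SD difference with SD 1. That needs well over 45 per group.

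At stake is the type II error of the primary comparison. The reader is told it is 20%. On the stated inputs it is about 35% for an unadjusted slope and about 23% with baseline adjustment.

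**Working it through.** **Inputs.** From Sample size and power calculation: two-sided alpha 0.05, power 0.80, seven measures, between-arm difference read as growing linearly from 0 to 0.5 SD, autoregressive correlation with r = 0.50 from first to last measure, 45 per group. From Procedure: 1:1 allocation. From the Abstract: assessments at the start of treatment and at 6, 12, 18, 24, 30 and 36 months, which makes seven equally spaced measures.

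**Correlation.** Six lags separate the first and last measures, so the adjacent correlation is 0.5^(1/6) = 0.891.

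**Variance of the slope over the whole follow-up, per patient, in SD².**
- Last minus first: 2(1 − 0.5) = 1.000.
- Generalised least squares slope from all seven measures: 0.9998. The five middle visits add almost nothing.
- Ordinary least squares weights: 1.089.
- First measure constrained equal across arms: 0.748.
- Covariance analysis of the last measure on the first: 1 − 0.5² = 0.750.

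**Attempt to reproduce 45.** With variance V, n per group = 2V(1.96 + 0.84)²/0.5². For V = 1 this is 2 × 7.85/0.25 = 62.8, so 63, or 64 with the t distribution. The stated 45 is not reproduced.

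**Power at 45 per group.** The standard error is √(2V/45). For V = 1 it is 0.211, so 0.5/0.211 = 2.37 and power is Φ(2.37 − 1.96) = 66%, or 65.0% with the noncentral t. A simulation of 20,000 trials gave 65.5% at 45 per group and 80.1% at 64.

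| Two-sided 0.05 test, stated inputs | Power at 45 | n per group for 80% |
|---|---|---|
| Generalised least squares slope | 65.0% | 64 |
| Ordinary least squares slope | 61.3% | 70 |
| Last minus first | 65.0% | 64 |
| Group-by-time F, epsilon-adjusted (epsilon 0.45) | 64.6% (simulated 59.7%) | 63 |
| Multivariate group-by-time test | 35% | 113 |
| Growth model, first measure constrained equal | 77.4% | 48 |
| Last measure with first as covariate | 77.3% | 49 |

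Correlation falling linearly to 0.50 also gives 64 for the generalised least squares slope. A one-sided slope test would need 51. The unadjusted group-by-time F nominally gives 89% at 45 and needs 37, but its simulated type I error is 9.8%, so it is not a 0.05 test.

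**What does come near 45.**
- Compound symmetry with r = 0.5: 42 per group with seven measures, 46 with six.
- An autoregressive process plus measurement error large enough to pull the adjacent correlation down to about 0.54: 45 per group, 81% power.

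Both are close to exchangeable, and neither is stated.

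**In effect-size terms.** At 45 per group the unadjusted slope has 80% power for 2.80 × 0.211 = 0.59 SD, not 0.50. The 95% confidence interval would have a half-width of about 1.96 × 0.211 = 0.41 SD.

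**The case against.** The strongest reply is that the power procedure comes from a cited text that is not at hand, and that the article does not say which effect was powered. The number 45 may have come out of a conventional routine, or from an autoregressive structure with measurement error, since only the first-to-last correlation is fixed. This stands as far as cause goes. A reader might infer that the authors made an arithmetic slip or used compound symmetry by mistake; the document does not show either. What it does show is a set of inputs from which none of the valid tests tried gives 45 at 80% power.

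The second reply is that 65% belongs to one model. Baseline adjustment is a detail that may sit in an analysis plan not shown here, and with it the gap shrinks to 3 or 4 patients per group. This also stands, and it is why the result is given as two figures. It narrows the gap but does not close it.

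A reader might also infer that the trial intends to treat a non-significant result as equality, because the Discussion says "If this were the case, health care resources should be devoted to the less costly variant". That sentence is conditional on the treatments truly being equally effective. It is not a rule for reading a p-value, and the Health economic evaluation section relies on bootstrap intervals and acceptability curves. Nor should the absence of an attrition allowance be counted as an error: the article gives no loss rate, describes active efforts to retain patients, and may leave inflation to the full protocol.

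**Conclusion.** The power statement is wrong as written for the planned slope comparison. On the stated inputs, 45 per group gives about 65% power without baseline adjustment (61% with ordinary least squares weights; 64 to 70 per group for 80%) and about 77% with the first of the seven measures constrained or adjusted for (48 to 49 per group for 80%).

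This rests on a pure first-order autoregressive correlation, a difference of zero at the first measure and 0.5 SD at the last, complete data, and no clustering by therapy group. If unstated measurement error were added while r = 0.50 is kept at the last lag, the unadjusted figure would lie between 65% and about 83%. It would be wrong to quote 65% as the trial's power without naming the model.

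**What to change.** 1. Restate the power at 45 per group, before attrition, as about 65% for an unadjusted slope or about 77% with baseline adjustment. Name the effect tested, the model and the full correlation matrix. If a measurement-error component was intended, state it.

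2. Make the primary growth model use baseline BSI, as a covariate or with baseline constrained equal, and say which assessment is meant. The 77% refers to the first of the seven measures, taken at the start of treatment. The Design and Procedure sections describe a separate assessment before randomization, whose correlation with 36 months is not given. If that one is used, state the assumed correlation. As an example, one further six-month lag (assumption) gives r = 0.5^(7/6) = 0.445, V = 1 − 0.445² = 0.80 and about 75% power. The earlier assessment is the one for which randomization itself justifies an equal-baseline constraint, because patients know their allocation by the start of treatment.

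3. Report the 95% confidence interval for the BSI difference, and say which differences it excludes, so that a non-significant result is not taken as equal effectiveness.

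The cost is some wording and one model term. Recruitment ended in June 2014, and no further patients are asked for. The stated power becomes less favourable.

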### Statistical analyses

First, to investigate potential differences between the two groups at baseline, we will use parametric and nonparametric descriptive statistics, as appropriate. For the main analyses concentrating on primary and secondary outcomes, linear growth curve models for normally distributed outcome measurements will be used, logistic regression for binary data, and Poisson regression models for ordinal data. Results will be expressed in terms of comparison of the slopes for interval data, odds ratios for binary data, and incidence rate ratios for ordinal data. Furthermore, we will perform explorative analyses regarding predictors of differential treatment outcome. All analyses will be conducted according to intention-to-treat principles.

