#### Secondary outcome measures

##### Parasuicidal behaviour

Suicide and self-harm are assessed with the Suicide and Self-Harm Inventory (SSHI) [3]. The SSHI is a semi-structured interview assessing (a) the frequency and severity of suicidal acts in the past 6 months, and (b) the frequency and severity of acts of self-mutilation in the past 6 months. Multiple acts of self-mutilation over a short period of time – for example, frenzied self-cutting – are counted as a single act.

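### Poisson regression and incidence rate ratios are assigned to ordinal data, which they do not suit, and the self-harm and suicide-act counts are given no named model

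*Protocol article*

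**What the plan says.** The Statistical analyses section of the protocol article sets the models by type of data. It opens with "For the main analyses concentrating on primary and secondary outcomes, linear growth curve models for normally distributed outcome measurements will be used" and continues with "logistic regression for binary data, and Poisson regression models for ordinal data". The following sentence gives the matching effect measures: slopes for interval data, odds ratios for binary data and "incidence rate ratios for ordinal data". Count data do not appear in either sentence, and no outcome is named as ordinal.

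Under Parasuicidal behaviour, the SSHI is said to record "the frequency and severity of suicidal acts in the past 6 months" and "the frequency and severity of acts of self-mutilation in the past 6 months". A counting rule is added: "Multiple acts of self-mutilation over a short period of time" are scored as one act. The article does not say how severity is graded.

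**The concern.** Poisson regression describes how many events occur over a period of exposure, and its coefficient is a log ratio of event rates. Ordered categories have no events and no exposure. Their codes carry order only, so a ratio of mean codes depends on how the categories happen to be numbered.

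The outcomes in this trial that are plainly counts, suicidal acts and acts of self-mutilation per 6 months, fall into none of the named data types. Parasuicidal behaviour is the first secondary outcome listed, and reducing it is one of the five general treatment goals. An analyst following the text literally would have no model for it. An analyst who reads ordinal as count would have no model for ordered categories. An analysis plan written faithfully from this section would inherit one gap or the other.

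**Working it through.** **1. The two sentences side by side.** The first pairs Poisson regression with ordinal data. The second pairs incidence rate ratios with ordinal data. The mismatch is therefore stated once for the model and once for the estimate.

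**2. Why the estimate has no fixed meaning for ordered categories.** Take two assumed four-level distributions, coded 0 to 3.
- Arm A has probabilities 0.4, 0.3, 0.2, 0.1. Mean = 0.3 + 0.4 + 0.3 = 1.0.
- Arm B has 0.25 at each level. Mean = 1.5.
- The rate ratio is 1.5/1.0 = 1.50.
- Recode the same categories 1 to 4. The means become 2.0 and 2.5, and the ratio is 2.5/2.0 = 1.25.

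The data are the same and the effect differs. A proportional-odds model uses order only and is unchanged by the recoding.

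**3. Plan's own figures.** The article gives no mean, variance or dispersion for any count or ordinal outcome, so there is nothing to reproduce on this point. The 45 per group rests on the BSI. A generalised least squares slope comparison with a common baseline and autoregressive correlation gives 47 per arm. Other readings of the same inputs give different numbers, but none bears on this point.

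**4. What plain Poisson would do to overdispersed counts (illustrative).** If the variance is phi times the mean, the Poisson standard error is too small by sqrt(phi). The true rejection rate of a nominal two-sided 5% test is 2(1 − Φ(1.96/sqrt(phi))).
- phi = 2: 1.96/1.414 = 1.386, giving 0.166.
- phi = 5: 1.96/2.236 = 0.877, giving 0.381.

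**5. Check by simulation.** Each scenario used 2000 null trials with 45 patients per arm and one negative binomial count per patient, with variance mu(1 + k·mu). All values of mu and k are assumptions.

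| mean mu | k | Poisson SE / true SE | type I error, Poisson | type I error, robust variance |
|---|---|---|---|---|
| 3 | 0 (no overdispersion) | 0.99 | 0.049 | 0.054 |
| 0.5 | 1 | 0.83 | 0.096 | 0.055 |
| 0.5 | 2 | 0.71 | 0.146 | 0.063 |
| 3 | 1 | 0.51 | 0.308 | 0.058 |
| 3 | 2 | 0.38 | 0.466 | 0.067 |
| 10 | 1 | 0.30 | 0.537 | 0.063 |
| 10 | 2 | 0.22 | 0.673 | 0.062 |
| 10 | 4 | 0.16 | 0.770 | 0.086 |

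With rare events the loss is modest. With frequent acts it is large. A robust variance largely restores the error rate, less fully at the most extreme dispersion.

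**6. Poisson on truly ordinal scores.** For assumed probabilities 0.1, 0.2, 0.3, 0.25, 0.15 on codes 0 to 4, the mean is 2.15 and the variance 1.4275. The ratio of Poisson to true standard error is sqrt(2.15/1.4275) = 1.23. For the two four-level distributions in step 2 it is sqrt(1.0/1.0) = 1.00 and sqrt(1.5/1.25) = 1.10. The error here is nil or conservative. The harm is an estimate that cannot be interpreted, not excess false positives.

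**The case against.** The strongest reply is that one word is wrong. Poisson and incidence rate ratios fit each other and fit the SSHI frequencies. If ordinal is read as count, both sentences make sense. That is the likeliest intention. It does not remove the point, because the word stands in both sentences and the substitution leaves ordered categories without a model. It does mean that the repair is small.

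A reader might also infer that the self-harm and suicide analyses will have standard errors far too small and produce false differences between arms. The documents do not support that:
- The article never assigns the SSHI to Poisson and never says the model will be fitted without allowance for overdispersion. Such handling commonly sits in the statistical analysis plan, which is not shown, so its absence is no finding.
- No dispersion is given, so every figure in steps 4 and 5 is conditional.
- Scoring a burst of self-mutilation as one act removes some of the high values that drive overdispersion.
- For rare events such as suicide attempts (assumed mean 0.3 to 0.5, k 0.5 to 2), the Poisson standard error is about 0.7 to 0.9 of the true one, which is too small but not far too small.

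Finally, no outcome is designated as ordinal. SSHI severity and the BDI bands are possible examples only: severity scoring is not described, and nothing says that the bands, rather than the total score, will be analysed. This objection stands. It cannot be said which outcome would receive an uninterpretable estimate.

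**Conclusion.** The stated rule is wrong and should be corrected. Poisson regression and incidence rate ratios do not suit ordinal data, and the section names no model for counts although the SSHI act frequencies are counts. This conclusion rests on the text alone.

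The effect on error rates is a conditional illustration. A nominal 5% test would have a type I error of about 17% at phi = 2 and 38% at phi = 5, if overdispersed counts were fitted by plain Poisson. Both the dispersion and the unmodified fit are assumptions.

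The reach is limited to secondary outcomes that are neither normally distributed nor binary. The BSI primary analysis uses a linear growth model and is untouched, as is the sample size. The point is a worthwhile correction of moderate weight and does not threaten the trial's main result.

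**What to change.** Correct both sentences in Statistical analyses.
- **Counts** (SSHI suicidal acts and acts of self-mutilation per 6 months): a count model that allows for overdispersion and for repeated measures on the same patient, reported as incidence rate ratios. Negative binomial with a patient random effect is one choice. Poisson with a robust variance clustered on patient is another.
- **Truly ordinal outcomes**, if any: a proportional-odds model allowing for repeated measures, reported as odds ratios.
- State which outcomes belong to each class, including how SSHI severity is treated.

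No offset for the recall period is needed. Recall is 6 months for everyone, so a constant offset shifts the intercept and leaves the rate ratio unchanged.

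The cost is a wording change, with no new data or patients. Where counts are overdispersed, intervals will be wider than under plain Poisson, as they should be.

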#### Health economic evaluation

We will estimate the difference in total costs for MBT-DH compared to MBT-IOP and the difference in clinically relevant effects of the treatments. By dividing the difference in costs by the difference in effectiveness, the incremental cost-effectiveness ratio (ICER) will be estimated. The ICER represents the extra amount of money that has to be invested to gain one extra unit of effect (or, conversely, the amount of money that will be saved if one unit of effect is lost).

In the economic evaluation, all relevant costs and effects will be taken into account. This means that we will use a so-called societal perspective, which is preferred in economic evaluations in the Netherlands [82]. The costs will include *all* costs, that is, intervention costs, direct and indirect medical costs, as well as productivity losses and costs accruing elsewhere in the health care system. From the societal perspective, clinically relevant effects are those effects that are meaningful for society. Moreover, in order to be able to compare effects between different interventions in health care, effects should be expressed in generic terms. We will therefore use QALYs and will express the cost-effectiveness of each intervention and the ratio between these cost-effectiveness estimates as cost per QALY. The use of QALYs is advised in guidelines for cost-effectiveness analysis, especially when main effects are expected in quality of life [82,83].

Our primary cost-effectiveness ratio will be estimated using empirical data only and therefore a 3-year time horizon will be used, which is equal to the trial duration. Cost data are generally highly skewed, and QALY scores and ICER values are not distributed normally in most cases. Therefore, the uncertainty intervals around the mean costs, mean effects and mean ICER values will be estimated using bootstrap simulations with at least 1000 replications [84-86]. These results will be graphically presented in a cost-effectiveness plane. Various societal willingness-to-pay values will be used to estimate net monetary benefits. These net monetary benefits are then used to derive cost-effectiveness acceptability curves.

We will also explore the long-term costs and effects of MBT-DH and MBT-IOP from a societal perspective. One way of achieving this would be to use a Markov model to explore the long-term cost-effectiveness of the intervention under study. However, in a Markov model, health stages are often predefined, discrete stages, which should reflect the biological or theoretical understanding of the condition being modelled [87,88]. Because in this trial the primary outcome measures, such as the BSI, are continuous measures, it will not be possible to create an unambiguous definition of health states to model disease progression. Using heterogeneous health states may be controversial, as it means that a wide range of patients may be clustered in one health state. In order to explore the cost-effectiveness of the interventions using a Markov model in our study, we will therefore define health states on the basis of a cut-off score on one of the outcome measures such as the BSI, in order to create discrete health stages. We will extend the cost-effectiveness model results after the duration of the trial using different assumptions based on, for example, the literature. Sensitivity analysis will be performed in order to investigate the influence of those assumptions on the model results.

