### Procedure

All patients referred to one of the mental health care centres are invited for a standard intake interview, which includes standardized assessment by means of the Structured Clinical Interview for DSM-IV Axis I disorders (SCID-I) [41] and SCID-II [39]. All patients eligible for MBT treatment (with a BPD diagnosis and aged ≥18 years) are given both written and verbal information about the study. Eligible patients are given 1 week to consider participation in the trial. Patients who are willing to participate in the study are asked to sign an informed consent sheet and complete the baseline assessment. Next, they are randomized to either MBT-DH or MBT-IOP by an independent researcher using a computerized 1:1 algorithm. Patients are informed about their treatment allocation and placed on a waiting list. One week prior to start of the main treatment phase, and subsequently at 6-months intervals up to 36 months after the start of treatment, patients complete an assessment battery as described below. Patients who are excluded from the trial on the basis of exclusion criteria, or who refuse to participate in the trial, are ideally assigned to an alternative evidence-based treatment. Excluded and refusing patients are asked to complete the baseline assessment only, for which they sign a separate informed consent form. At 18 and 36 months, the SCID-I and SCID-II are re-administered by MSc-level psychologists. Extensive efforts are being made to collect data at the follow-up time points by means of an outreaching approach towards patients: patients are contacted by telephone, e-mail and letters (with reminders as necessary) to motivate them to attend assessments, and home visits are made if necessary.

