##### Quality of life

Quality of life is measured using the EuroQol EQ-5D-3 L [62]. This self-report questionnaire provides a simple method to capture health problems according to a five-dimensional classification: mobility, self-care, usual activities, pain/discomfort, and anxiety/depression. Each dimension is divided into three levels: no problem, moderate problems, and extreme problems. The five dimensions can be summarized into a “value”, based on the preferences of the general public. These values can be used as societal weights for the calculation of Quality Adjusted Life Years (QALYs) in health economic evaluations (see also below). To calculate these societal weights, we used a Dutch validation study [63]. Adjacent to the five dimensions, the EuroQol presents a vertical visual analogue scale, ranging from 0 (worst imaginable health) to 100 (best imaginable health), on which the respondent marks the point that they feel represents their current health. The values on this scale are seen as representing patients’ values, in contrary to the societal weight based on the five dimensions. The reliability of the EQ-5D-3 L has been investigated and found to be acceptable [64], and it has shown to be sensitive to change in patients with personality disorders [14,65].

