##### Costs

The intervention costs of MBT-DH and MBT-IOP will be calculated using a mixture of top-down and bottom-up approaches. The intervention costs estimates will include personnel costs, implementation costs (e.g., hosting and coaching), and any other overhead costs associated with the treatment. Medical costs beyond the intervention costs specific to MBT-DH and MBT-IOP will be calculated using the Trimbos and Institute for Medical Technology Assessment Questionnaire on Costs Associated with Psychiatric Illness (TiC-P) [74-76]). The TiC-P will be used to measure health care utilization at baseline and after 6, 12, 18, 24, and 36 months.

The first part of the TiC-P consists of questions on (1) the number of visits to, for example, a general practitioner, psychiatrist (outside MBT-DH or MBT-IOP), medical specialist, physiotherapist or alternative health practitioner; (2) the day care/hospital lengths of stay (outside MBT-DH or MBT-IOP); and (3) the use of medication in the 4 weeks prior to filling out the questionnaire [74]. These values are multiplied by the unit prices of the corresponding health care services according to the Dutch manual for costing studies in health care [76,77]. The unit prices will be adjusted to 2014 prices using the Consumer Price Index [78]. As the mean direct costs are measured per 4 weeks, we will multiply these values by 13 to obtain estimates for the annual costs.

The Tic-P also asks the patient to report any productivity losses, that is, absence from work or reduced productivity at work. This is used to estimate the so-called “friction costs”, that is, the monetary representation of the replacement of the labour. The friction-cost method takes the employer's perspective and counts as “lost” only those hours not worked until another employee takes over the patient's work. This is a more conservative estimate than the so-called “human capital method”, which relates productivity costs to the labour costs of the patient on a one-to-one basis. The choice between friction costs and human capital is still a subject of debate among economists. In this study, we chose the more conservative friction-cost method [79,80].

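### As described, the incremental costs and QALYs are a comparison of arm means with no baseline adjustment; adjusting for baseline utility would give a more precise QALY difference at almost no cost

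*Protocol article*

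**What the plan says.** The Health economic evaluation section sets out the calculation in order. It starts with the two contrasts: "We will estimate the difference in total costs for MBT-DH compared to MBT-IOP and the difference in clinically relevant effects of the treatments". It then forms the ratio: "By dividing the difference in costs by the difference in effectiveness, the incremental cost-effectiveness ratio (ICER) will be estimated". For uncertainty, "the uncertainty intervals around the mean costs, mean effects and mean ICER values will be estimated using bootstrap simulations with at least 1000 replications". The cost-effectiveness plane, net monetary benefits and acceptability curves follow from those replicates. The horizon is three years, and the effect unit is the QALY, built from EQ-5D-3L values (Quality of life section).

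No regression model or covariate appears at any of these steps. The Statistical analyses section names models for the clinical outcomes but deals with baseline differences between arms only descriptively, and it is not linked to the economic calculation.

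On baseline data, the Costs section is explicit: "The TiC-P will be used to measure health care utilization at baseline and after 6, 12, 18, 24, and 36 months". For EQ-5D no schedule is given. The Procedure section says of the period before randomization: "Patients who are willing to participate in the study are asked to sign an informed consent sheet and complete the baseline assessment". It does not list what that assessment contains.

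**The concern.** A three-year QALY total is an area under repeated EQ-5D values. A patient who starts with higher utility tends to stay higher, so baseline utility is likely to be a strong predictor of the total. A comparison of mean QALYs leaves that predictable variation in the error term. The interval is then wider than it need be, and whatever difference in starting utility the randomization happened to produce is carried into the QALY difference.

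Two features make this matter here. Cost-effectiveness is the trial's second stated aim, yet the sample size was set for the BSI at 45 per group. In addition, the QALY difference is the denominator of the ICER, and the Discussion allows that the two programmes may be equally effective. A small denominator makes the ratio sensitive to modest shifts. The same shift passes into net benefit, the plane and the acceptability curves.

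**Working it through.** **Inputs from the article.** 45 per group (Sample size and power calculation), three-year horizon, assessments every 6 months from start of treatment to 36 months. For the BSI only: autoregressive correlation with 0.50 between baseline and last follow-up, and a linear divergence of 0.5 SD.

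The article gives no figure for the economic analysis that could be reproduced. The 45 per group is taken as the planned size. Standard formulas did not return it exactly (63 per arm for a simple comparison of means, 48 with baseline adjustment at r = 0.5), but the settings of the cited procedure are not shown and nothing below depends on this.

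**Assumptions, not in the article.** EQ-5D SD 0.25 (range 0.20 to 0.30). EQ-5D correlation either exchangeable at 0.3, 0.4 or 0.5, or the BSI autoregressive structure, with step rho = 0.5^(1/6) = 0.891. The covariate is a pre-randomization utility; in the autoregressive case it is placed one 6-month step before the first value in the area.

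**Step 1: chance imbalance.** The SE of a baseline mean difference is sqrt(2/45) = 0.211 SD. The probability of an imbalance above 0.2 SD in either direction is 34%. In utility units one SE is 0.25 × 0.211 = 0.053.

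**Step 2: QALY variance.** Trapezoid weights over seven values are w = (0.25, 0.5 five times, 0.25), which sum to 3 years, with sum of squares 1.375. In SD² units:

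- Exchangeable: Var = 1.375 + r(9 − 1.375), and covariance with baseline = 3r.
- Autoregressive: Var = w′Rw = 7.22, and covariance = Σ w_k rho^(k+1) for k = 0 to 6, which is 1.93.

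R² = covariance² / Var. The SE of the QALY difference is 0.25 × sqrt(Var × 2/45). The adjusted SE multiplies this by sqrt(1 − R²). The shift for a one-SE imbalance is covariance × 0.0527.

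| Correlation | Var | Cov | R² | SE unadjusted | SE adjusted | SE cut | Shift (QALY) |
|---|---|---|---|---|---|---|---|
| Exchangeable 0.3 | 3.66 | 0.90 | 0.22 | 0.101 | 0.089 | 12% | 0.05 |
| Exchangeable 0.4 | 4.43 | 1.20 | 0.33 | 0.111 | 0.091 | 18% | 0.06 |
| Exchangeable 0.5 | 5.19 | 1.50 | 0.43 | 0.120 | 0.090 | 25% | 0.08 |
| Autoregressive | 7.22 | 1.93 | 0.52 | 0.142 | 0.099 | 30% | 0.10 |

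R² and the percentage cut do not depend on the SD. The SEs and shifts scale with it: over SD 0.20 to 0.30 the shift runs from 0.04 (SD 0.20, exchangeable 0.3) to 0.12 (SD 0.30, autoregressive).

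**Step 3: scale.** If the BSI divergence of 0.5 SD were transferred to EQ-5D, the QALY difference would be ½ × 3 years × (0.5 × 0.25) = 0.19. A one-SE imbalance would then be roughly a quarter to a half of that effect. In sample-size terms, 45/(1 − R²) gives an unadjusted equivalent of about 58 to 93 per arm.

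**Step 4: effect of the assumed gap.** Without the 6-month gap, so that the covariate is itself the first value in the area, the autoregressive covariance is 2.17 and R² is 0.65. Including the gap therefore lowers the gain rather than inflating it.

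No corresponding calculation is possible for costs, because the article gives neither a cost SD nor a cost correlation.

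**The case against.** The strongest objection is that silence is not a decision. The article never says raw, crude or unadjusted. A difference in costs and QALYs can be regression-adjusted and bootstrapped without contradicting a word of it, and a condensed article may leave covariates to a fuller plan. A reader might infer that the investigators have chosen an unadjusted analysis; the text does not support that. What remains is that the section specifies the calculation from contrast to acceptability curve with no adjustment at any step, so an analyst following it would compare arm means. A better estimator is available for the same data.

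A reader might also infer that the ICER would be biased. It would not be in the usual sense: allocation is randomized 1:1, and chance imbalance is part of the sampling variability that the bootstrap intervals cover. The loss is of precision, together with the carry-over of whatever imbalance actually occurs.

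Three further objections stand as limits:

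- That EQ-5D is measured before randomization is implied by the baseline assessment but not stated. The TiC-P baseline is stated, but not whether it precedes randomization.
- The EQ-5D SD and correlations are assumed, the autoregressive structure is borrowed from the BSI, and the 0.19 QALY comparator transfers a BSI effect to another instrument.
- The cost side has no numbers. Programme cost is set largely by arm, and direct costs are measured over 4 weeks, so baseline cost is probably a weaker predictor than baseline utility.

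**Conclusion.** The point holds as an improvement to the estimator, not as an error or a source of bias. Followed as written, the economic analysis compares arm means and gives up precision that baseline utility would supply. Under the stated assumptions the SE of the QALY difference would fall by about 12% to 30%, and a one-SE imbalance in baseline utility would move the unadjusted difference by about 0.05 to 0.10 QALY at an SD of 0.25. The direction is secure as long as EQ-5D values are positively correlated over time; the size rests on an SD and correlations that the article does not give. The effect on the ICER itself cannot be computed from the article. For costs, only a smaller and unquantified gain can be expected.

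**What to change.** In the Health economic evaluation section, state that incremental QALYs are estimated by regression on arm and baseline EQ-5D utility. Use the pre-randomization value if EQ-5D is in that battery, and say so explicitly; the value taken just before treatment comes after patients know their allocation and have entered pretreatment. Estimate incremental costs in the same way with baseline TiC-P cost, for example jointly with QALYs by seemingly unrelated regression. Refit both in every bootstrap replicate, so that the ICER, net monetary benefit, plane and acceptability curves all use the adjusted differences. Report the unadjusted result alongside.

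The cost is a sentence or two of text and a few lines of code. No patient procedure changes, and no new data are needed provided baseline EQ-5D was collected as the article implies. If adjustment is already specified in a fuller plan, a sentence saying so settles the point.
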